### Safety analysis

All adverse reactions that have occurred are presented by severity and causal relationship with the test drug, and the incidence rates of adverse reactions, adverse reactions that caused dropout, and serious adverse reactions are analyzed. For clinical trial subjects who dropped out due to treatment failure or adverse reactions, the proportion of each group is presented along with a 95% confidence interval. Chi-square analysis or Fisher's exact test is performed on the observed and expected frequencies.

The mean differences in AST, ALT, ALP, TB, GGT, BUN, creatinine, and eGFR levels at baseline, week 4, and week 8 are compared. If the assumption of normality is satisfied, an independent t-test is performed, and if the assumption of normality is not met, a Mann–Whitney U test is conducted. However, if a significant difference between the groups is found in the baseline values of AST, ALT, ALP, TB, GGT, BUN, creatinine, and eGFR, an ANCOVA is performed. The missing values are estimated and replaced using the stochastic regression imputation method.

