#### Exclusion criteria

Patients with co-morbidities such as pneumonia, interstitial lung disease, and active pulmonary tuberculosis on chest X-ray examinationPatients who have been using maintenance therapy with oral steroids, anti-IgE antibodies, or herbal medicines for asthma treatment since 4 weeks ago.Patients with aspartate aminotransferase (AST)/alanine aminotransferase (ALT) levels exceeding twice the normal limit, or with an estimated glomerular filtration rate (eGFR) of less than 60 mL/min/1.73 m^2^ (However, for those aged 65 and over, individuals with an eGFR less than 45 mL/min/1.73m^2^)Chronic heart failure of class III or IV (New York Heart Association)Patients with alcohol or other substance abuse/dependency or historyPatients with malignant tumors or a history of malignant tumors (however, if they have not recurred for more than 5 years, participation is possible).Patients with a history of hypersensitivity reactions or allergies to research-related drugsPatients who are unable to read and write or have cognitive impairmentPregnant or lactating women Patients who participated in other clinical trials within recent 30 days before this clinical trial (based on the date of written consent) If the researcher determines that it is inappropriate to participate in clinical research due to other reasons

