### Safety assessment

Laboratory tests (liver function test, blood urea nitrogen (BUN), creatinine, eGFR, sodium, potassium, and chloride) and vital sign measurements will be conducted before drug administration and 4 and 8 weeks after administration. During the 2nd and 6th weeks of drug administration, adverse reactions will be checked via phone visits to evaluate any adverse reactions associated with the drug administration during the test period. If an adverse reaction occurs, a trial participation meeting will be held to estimate its association with the clinical drug.

To test the safety of the herbal medicine intake, AST, ALT, alkaline phosphatase (ALP), total bilirubin (TB), gamma glutamyl transferase (GGT), BUN, creatinine, and eGFR are measured. To check for damage to liver function caused by herbal medicine, AST, ALT, ALP, TB, and GGT levels are measured. This indicator was structured with reference to the herbal medicine-induced liver injury investigation forms to improve the research quality of herbal safety presented by Yoon et al. (2009) [19]. The presence of kidney function damage caused by herbal medicine intake is confirmed by BUN, creatinine, and eGFR.

Adverse events (AEs) refer to undesirable and unintended signs, symptoms, or diseases that occur during a clinical trial and do not necessarily have to be causally related to the treatment used in the clinical trial. Serious adverse events (SAEs) refer to medical situations that are of significance, including death, life-threatening situations, need for hospitalization or extension of hospitalization, permanent or severe disability and impairment, and congenital anomalies or abnormalities occurring in the fetus, among the AEs that occur in the clinical trial participants during the clinical trial.

Continuous AE monitoring is conducted for all participants throughout the trial period. If the person in charge of the clinical trial determines a clinically significant change through an objective examination, subjective symptom questioning, and blood tests, it is considered an AE. The researcher records all information related to the AE and SAE in the CRF, including the AE name, occurrence date, end date, intensity, correlation with the investigational drug, outcome, treatment status, and SAE status.

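### The liver and kidney tests are meant to find organ damage, but the stated analysis of means or ranks responds poorly to large changes in a few patients

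*Protocol article*

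**What the plan says.** The Safety assessment section of the protocol article states what the tests are for. On the liver: "To check for damage to liver function caused by herbal medicine, AST, ALT, ALP, TB, and GGT levels are measured". On the kidney: "The presence of kidney function damage caused by herbal medicine intake is confirmed by BUN, creatinine, and eGFR".

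The Safety analysis section then fixes how the values are analysed. The quantities compared at baseline, week 4 and week 8 are "The mean differences in AST, ALT, ALP, TB, GGT, BUN, creatinine, and eGFR levels". The test is an independent t-test if normality holds, and "if the assumption of normality is not met, a Mann–Whitney U test is conducted". ANCOVA replaces these if the baseline values differ significantly. On missing data: "The missing values are estimated and replaced using the stochastic regression imputation method". The section names no count of participants beyond a limit and no shift from baseline.

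There is a second route for an abnormal value. Under Safety assessment, "If the person in charge of the clinical trial determines a clinically significant change" on examination, questioning or blood tests, that change is an adverse event and is recorded. The Safety analysis section presents adverse reactions by severity and causality and analyses their incidence, including those that are serious or lead to dropout.

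A numeric limit for liver enzymes does appear in the article, but only at entry: the Exclusion criteria bar patients with AST/ALT "levels exceeding twice the normal limit".

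**The concern.** The stated purpose is a question about individual patients: did anyone's liver or kidney suffer? The stated analysis answers a question about the arms: did the average or the typical rank move? If a product harms a small number of people and leaves the rest unchanged, the two questions have different answers. The arm mean moves by a few units and the rank distribution hardly moves at all.

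The rule for choosing the test makes this worse. Liver enzymes are usually right-skewed, and a few very high values add to the skew. The patients of interest therefore help to push the comparison to the rank test, which limits the influence of extreme values by design.

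The Discussion makes proven safety one of the conditions for adding the product to standard asthma treatment. The Economic evaluation section chooses cost-minimization when the arms do not differ, side effects included. A non-significant laboratory comparison could be read as support for both.

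**Working it through.** **Inputs from the protocol article.** Two-sided α = 0.05 and 1:1 allocation. There are 168 evaluable participants, and allowing for 15% dropout gives 168 / 0.85 = 197.6, so 198. That is 99 per arm randomized and 84 per arm evaluable. The article gives no figure for the laboratory comparison itself, so there is none to reproduce.

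**Assumptions, not in the article.** ALT is lognormal with mean 25 and SD 10 U/L. This gives log-SD = √ln(1 + (10/25)²) = 0.385 and log-mean = ln 25 − 0.385²/2 = 3.145. In the treated arm k patients are set to 200 U/L, which is 5 times an assumed upper limit of 40. No patient in the placebo arm is affected.

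**Shift in the arm mean.** k × (200 − 25) / 99: for k = 3 it is 5.3 U/L, and for k = 6 it is 10.6 U/L.

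**Chance of p < 0.05, by simulation, 99 per arm**

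| k | Mann–Whitney | t-test | Fisher p, k/99 v 0/99 |
|---|---|---|---|
| 3 | about 6% | about 20% | 0.246 |
| 4 | about 7% | about 43% | 0.121 |
| 5 | about 9% | about 69% | 0.059 |
| 6 | about 10% | about 90% | 0.029 |

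Repeat runs agree to within a percentage point or two, so Mann–Whitney lies at about 6–11% over the whole range. With 84 per arm it is again 6–11%.

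**Which test would be used.** The article does not say how normality is judged. If a Shapiro–Wilk test at 0.05 is assumed, normality is rejected in every simulated trial with k ≥ 3, and in about 97% even with no injured patient. Under these assumptions the Mann–Whitney column is the one that applies.

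**Sensitivity to the assumed distribution.** Take instead median 22, log-SD 0.45, upper limit 40, and rises to 3, 5 or 10 times the limit, with 99 per arm:
- k = 1: Mann–Whitney about 5%, t-test 0.6–5%
- k = 2: Mann–Whitney 5–6%, t-test 2–8%
- k = 3: Mann–Whitney 6–7%, t-test 13–19%
- k = 5: Mann–Whitney 7–8%, t-test 40–91%

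**What a count would show.** 3/99 = 3.0%, exact 95% CI 0.6 to 8.6%. For 0/99 the exact upper limit is 1 − 0.025^(1/99) = 3.7%. The two intervals overlap and Fisher's p is 0.25, but the three cases are in the table.

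**The case against.** A reader might infer that liver and kidney safety is judged only by arm averages, so that the trial could not show injury in a few patients at all. The article does not support that. Monitoring for adverse events is continuous and covers every participant. A blood-test change judged clinically significant becomes an adverse event, and adverse reactions are analysed by incidence. A value of 200 U/L would probably be judged significant, and the judgement is made blind to arm. Nor is the t-test powerless: where it applies, it detects 5 or 6 such patients in most simulated trials.

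It can also be said that the proposed count is a weak test, that laboratory categories and shift tables often sit in a full protocol or SAP not shown here, and that entry criteria are not definitions of injury.

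Much of this stands, and it limits the point to the analysis of the laboratory values. Three things remain:
- The adverse-event route depends on judgement at several sites, with no numeric limit stated.
- Safety assessment defines adverse events regardless of cause, while Safety analysis tabulates adverse reactions. It is unclear whether an elevation judged unrelated to the product would be counted. Sorting by causality suggests that a broad meaning may be intended, but the article does not say so.
- This is more than silence. The article states the summary, the tests, the rule for choosing between them and the imputation, and that method suits its stated purpose poorly.

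The objection to entry limits is right for eGFR. A participant who enters just above the cut-off can cross it through ordinary variation, while a large fall from a high value would not count.

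**Conclusion.** The point holds for the laboratory analysis as the article fixes it. Means, ranks or ANCOVA on partly imputed values respond poorly to large changes in a few patients, although the tests are there to find liver and kidney damage. For 3 to 6 affected patients of 99, Mann–Whitney rejects in about 6–11% of simulated trials, against a false-positive rate of 5%.

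The size rests on assumed ALT distributions, an assumed upper limit, assumed numbers of affected patients, and skew sending the analysis to the rank test. No kidney analyte was simulated. For those the argument is one of principle, without a figure.

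The stronger conclusion, that such injuries would go unreported, does not follow, because the adverse-event route exists. Nor would a count be a more powerful test: Fisher's p is 0.25 for 3 v 0 and falls below 0.05 only at 6 v 0. What a count adds is that each case is visible, with an interval, by a rule set in advance. This is a cheap and worthwhile improvement.

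**What to change.** In the Safety analysis section, add for each analyte the number and percentage of participants per arm whose worst observed post-baseline value passes a pre-specified limit. Use observed values only, not imputed ones.
- For the liver tests, use pre-specified multiples of the upper limit of normal. For AST and ALT, start at the twice-normal level already used at entry.
- For eGFR and creatinine, use a pre-specified change from baseline rather than the entry cut-off.
- Give exact 95% confidence intervals and a baseline-to-worst shift table.
- Keep the mean comparisons as description.
- State whether the incidence tables cover all adverse events or only those judged related to the product.

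The cost is one or two descriptive tables from data already collected at weeks 4 and 8. Nothing in treatment or follow-up changes. If the full protocol or SAP already contains these tables, the Safety analysis text need only be aligned with it.

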#### Withdrawal criteria

Cases where the participant received treatments that could influence the study outcomes without the researcher's instructions during the study periodCases where the participant did not adhere to the clinical trial protocol or the compliance was below 70%Cases where the participant experienced adverse reactions that made it difficult to continue the clinical trial or where severe adverse reactions occurredCases where the participant withdrew their consentCases where the participant used additional drugs or any herbal medicine that could affect asthma treatment during the clinical trial (excluding temporary short-term use for treating acute exacerbation of asthma)Cases where the LTRA prescription was changed after the participant's registrationOther reasons deemed by the researcher as inappropriate for the continuation of the clinical trial

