### Statistical analysis

#### Effectiveness outcomes

Statistical analyses are conducted independently by a statistical expert using SAS. In the two-tailed tests, the level of significance is set at 0.05. All analyses primarily utilize intention-to-treat analysis, with per-protocol analysis conducted concurrently, and the results are presented together. In the demographic baseline data, continuous variables are presented as mean and standard deviation and are analyzed using an independent t-test or Mann–Whitney U test. Categorical variables are presented as frequency and proportion and analyzed using a chi-square test or Fisher's exact test (when the expected frequency is less than 5 in more than 25% of all values).

The primary efficacy evaluation is based on the mean change in FEV_1_ scores evaluated at week 8 (56 days post-dosing), whereas secondary efficacy evaluations compare the means of PEF, FVC, FEF25–75, FeNO, ACT scores, AQLQ scores, Serum IgE, eosinophil count, CRP, and the frequency of rescue medication use assessed at baseline and weeks 4 and 8. If the assumption of normality is satisfied, an independent t-test is conducted; otherwise, the Mann–Whitney U test is applied. However, if significant differences between the groups are found in baseline values, an analysis of covariance (ANCOVA) is performed. Missing data is replaced using the last observation carried forward method; each missing value is replaced with the participant's last observed value. For the secondary efficacy evaluation, the distribution of participants according to each diagnosis of Korean medicine pattern identification assessed at baseline is presented as frequency and proportion and visualized in tables or graphs through descriptive analysis.

Subgroup analysis will be performed according to the following criteria: First, subgroups will be divided according to the type of asthma medication (ICS or ICS + LABA) taken in addition to the LTRA at enrollment. Second, the effect will be further analyzed by age, separating younger patients (< 35 years) from older patients (> 60 years). Third, subgroups will be defined as male and female. Fourth, subgroups will be created based on severity as measured by ACT, ≤ 15 and > 15. Finally, subgroup analyses will be performed according to Korean medicine pattern identification.

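### Missing liver and kidney values are filled by a single random draw and then tested as if measured, so lab p-values run somewhat too small or the arm difference is diluted

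*Protocol article*

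**What the plan says.** Under Safety analysis, the protocol article states: "The mean differences in AST, ALT, ALP, TB, GGT, BUN, creatinine, and eGFR levels at baseline, week 4, and week 8 are compared". The test is chosen by distribution: "If the assumption of normality is satisfied, an independent t-test is performed, and if the assumption of normality is not met", a Mann-Whitney test is used, with ANCOVA if the arms differ at baseline. The paragraph closes with the missing-data rule: "The missing values are estimated and replaced using the stochastic regression imputation method".

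The general rules stand under Effectiveness outcomes. On error level: "In the two-tailed tests, the level of significance is set at 0.05". On analysis sets: "All analyses primarily utilize intention-to-treat analysis, with per-protocol analysis conducted concurrently, and the results are presented together".

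Two other sections bear on why labs may be missing. Under Safety assessment, a lab change can itself become an adverse event: when the person in charge "determines a clinically significant change through an objective examination, subjective symptom questioning, and blood tests, it is considered an AE". The Withdrawal criteria then include cases where "the participant experienced adverse reactions that made it difficult to continue the clinical trial". The laboratory tests and "vital sign measurements will be conducted before drug administration and 4 and 8 weeks after administration", so a participant who leaves after week 4 normally has a baseline and a week-4 value but no week-8 value.

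**The concern.** Stochastic regression imputation replaces a missing value by a fitted value plus one random residual. It is a single-imputation technique by definition. The completed data then enter an ordinary two-sample test that counts every filled-in value as an independent measurement.

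One of two things goes wrong, depending on whether arm is a predictor in the imputation model. They are alternatives and do not add up.

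- **Arm included.** The estimate is sound if the week-4 value is also used, but the reported standard error ignores the imputation uncertainty. The 5% test rejects too often.
- **Arm left out.** The 5% level holds when labs are missing completely at random, but imputed values in both arms are drawn towards a common mean and a true difference shrinks. For labs collected to detect liver and kidney harm from an herbal product, this is the more troubling direction.

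The fault is not that the article omits the imputation model, which it may leave to another document. The fault is that the method it does name, followed by the tests it does name, gives a faulty comparison either way.

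**Working it through.** **Inputs.** From the documents: 198 randomised 1:1, so n = 99 per arm; two-sided 0.05; labs at baseline, week 4 and week 8. Assumed: a fraction m of week-8 values missing, with m = 0.15 borrowed from the dropout allowance under Sample size (the documents give no lab missing rate) and m = 0.05 as a contrast; values standardised to SD 1; equal correlation ρ between visits of 0, 0.5, 0.7 or 0.9; week 4 observed for everyone when used as a predictor. The plan gives no figure of its own for this imputation to reproduce.

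**Arm included, missing completely at random.** The imputation model has arm, baseline and week 4, with R² = 2ρ²/(1 + ρ). In large samples:

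- The regression-based arm mean has n × variance = R² + (1 − R²)/(1 − m).
- The drawn residuals add m(1 − R²).
- Total: 1 + (1 − R²)·[m/(1 − m) + m]. The ordinary test assumes 1.
- So true SE / reported SE = √{1 + (1 − R²)·[m/(1 − m) + m]}, and the rejection rate is 2·[1 − Φ(1.96/ratio)].

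For m = 0.15 the bracket is 0.1765 + 0.15 = 0.3265. The reported SE is √(2/99) = 0.142 SD.

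| ρ | 1 − R² | SE ratio | Rejection under no difference |
|---|---|---|---|
| 0 | 1.000 | 1.152 | 8.9% |
| 0.5 | 0.667 | 1.104 | 7.6% |
| 0.7 | 0.424 | 1.067 | 6.6% |
| 0.9 | 0.147 | 1.024 | 5.6% |

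A simulation of this case with 20,000 replicates gives 8.9%, 7.6%, 6.6% and 5.6%. Smaller simulations gave 8.7–9.1%, 7.2–8.1%, 6.7–6.9% and 5.1–5.9%.

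With arm and baseline only, R² = ρ², and the same formula gives 8.9%, 7.9%, 7.0% and 5.7%. A Mann-Whitney test on lognormal values (log SD 0.4, imputed on the raw scale with arm, baseline and week 4) gave 8.9%, 7.4%, 6.5% and 5.8% by simulation.

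For m = 0.05 the bracket is 0.0526 + 0.05 = 0.1026, and rejection with week 4 in the model falls to 6.2%, 5.8%, 5.5% and 5.2%.

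**Arm left out, true difference 0.40 SD at weeks 4 and 8, m = 0.15.**

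- Baseline only: imputed values carry no arm difference, so the estimate is 0.85 × 0.40 = 0.34 SD at every ρ. Simulated power is 65–67%, against 72–74% using observed values only.
- Baseline and week 4: the week-4 coefficient, with the between-arm variance 0.40²/4 = 0.04 folded in, is b = (ρ + 0.04 − ρ²)/(1.04 − ρ²) = 0.04, 0.37, 0.45, 0.57. The estimate is 0.40 × (0.85 + 0.15b) = 0.34, 0.36, 0.37, 0.37 SD. Simulated power is 66%, 72%, 72%, 74%, so little is lost once week 4 is informative.

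**Dropout that follows a raised week-4 lab.** This was simulated with CSBHT dropout rising with the week-4 value (logit slope 1.5 per SD), about 15% missing per arm, control missing at random, and ρ = 0.5, 0.7, 0.9.

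| Analysis | Estimate of a true 0.40 SD | Rejection under no difference |
|---|---|---|
| Observed values only | 0.31, 0.28, 0.24 | 9.3%, 12.6%, 18.0% |
| Single draw: arm, baseline, week 4 | 0.40 each | 7.6%, 6.8%, 5.6% |
| Multiple imputation: same predictors | 0.40 each | 4.9%, 5.1%, 5.0% |

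A single draw with arm and baseline but not week 4 gives 0.36, 0.36 and 0.38. Under missing completely at random at 15%, multiple imputation (20 draws, Rubin's rules) rejects 5.1%, 4.6%, 4.9% and 5.3% at ρ = 0, 0.5, 0.7, 0.9.

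**The case against.** The strongest reply is that the harm is small where it is most likely to arise. Repeat values of the same lab in the same person are seldom uncorrelated, and the figures near 9% need a correlation of 0. At 0.7 to 0.9, with arm and week 4 in the model, rejection is 6.6% to 5.6%. Across the eight week-8 tests that adds 8 × 0.016 = 0.13 to 8 × 0.006 = 0.05 expected false positives, beside the 16 × 0.05 = 0.8 already expected from sixteen unadjusted tests at weeks 4 and 8. No stopping rule or decision in the article rests on a lab p-value, and clinically significant lab changes are also caught per participant as adverse events. All of this stands, and it is why the point is minor.

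It is also true that the named method can beat the simple alternative. If withdrawal follows a raised week-4 lab, a single draw with arm, baseline and week 4 is unbiased while the observed-only comparison is not. That stands, and it argues against replacing imputation by deletion.

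A third reply is that the direction of the error depends on an imputation model the article does not give. That is correct, but neither version gives a sound comparison, and the ordinary tests named in the same paragraph leave no place for pooling. If multiple imputation was intended, the sentence names the wrong method.

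The concurrent per-protocol run does not rescue the comparison. It would probably contain few imputed labs, but it leaves the intention-to-treat p-values as they are. The sentence making intention-to-treat primary sits under Effectiveness outcomes, although it is worded to cover all analyses.

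**Conclusion.** The concern holds and is minor. At 15% missing, the single draw with arm in the model makes the reported standard error too small: the true one is about 2% to 15% larger, and the 5% test rejects about 5.6% to 8.9% of the time, with the lower end the more plausible for well-correlated labs. With arm left out, a true 0.40 SD difference is estimated as 0.34 to 0.37 SD. At 5% missing the inflation is at most about one percentage point.

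These figures rest on an assumed missing rate, normal data with equal correlations, and missingness at week 8 only. The conditional ANCOVA was not simulated. The dropout scenario tied to week 4 is an illustration, not something the documents state. The primary FEV1 analysis and the adverse-reaction tables do not use this imputation.

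**What to change.** Replace the imputation sentence under Safety analysis with wording such as: missing post-baseline laboratory values are handled by multiple imputation with arm, baseline and week-4 values in the model, and arm differences are pooled by Rubin's rules. For skewed labs, impute and compare on the log scale, because a Mann-Whitney p-value has no standard error to pool. Report observed-value summaries alongside, with the number measured per arm at weeks 4 and 8. An observed-only analysis should not be the sole replacement. A summary of each participant's worst post-baseline value is optional.

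The cost is one or two sentences and a little more programming, with no new data or visits. The price is honest, larger standard errors: at 15% missing, 0.155 SD at correlation 0, 0.148 at 0.7 and 0.144 at 0.9, against 0.142 from the single draw. Multiple imputation does not remove bias if dropout depends on a lab value that was never measured.
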